### Interventions

#### Lifestyle interventions

The participants in both groups will receive health education about diet and exercise according to the Guidelines for the Prevention and Treatment of Dyslipidemia in Chinese Adults (revised in 2016) [24]. Regulation of diet and exercise of the subjects will be regarded as very important in this study. A standardized meal suggestion (30 kcal/kg ideal weight/day) will be provided, which includes a reasonable match of calories, protein and carbohydrates, low-cholesterol, low-salt, and low-sugar diet. Individuals will be recommended to do moderate-intensity metabolic exercise for 30 min, 5–7 days a week. Participants will be asked to be strict about their diet and to avoid short-term or high-intensity exercise. Risk factors, such as smoking and alcoholism, will be controlled strictly. Investigators will emphasize the importance of diet and exercise interventions at each treatment visit.

#### Pharmacologic treatments

A total of 118 patients with primary dyslipidemia will undergo baseline data acquisition and lifestyle guidance and be randomly assigned into two groups: BBR (0.5 g, twice daily) or placebo. BBR or placebo will be administrated orally for 12 weeks. BBR and placebo were produced by the same pharmaceutical company (Shanxi Zhendong Pharmaceutical Co., Ltd. Lot No.:20190301). They have the same appearance, size, odor, and taste.

During each visit, the observer needs to record in detail whether the patient takes the medicine on time, and withdraws the residual drugs, so as to assess the patient’s medication compliance: drug compliance = actual total amount of medicine taken/total amount of medicine required by the protocol × 100%. Any drug administered during the study must be recorded and described in detail in CRFs, including the specific type of drug (trade name or generic name), the indications for use, the date, and the dose. Any lipid-lowing therapy except for the experimental drugs will be banned or restricted during the study.

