## Background

Dyslipidemia is characterized by increased plasma total cholesterol (TC), low-density lipoprotein cholesterol (LDL-C), triglyceride (TG), or decreased high-density lipoprotein cholesterol (HDL-C). It is the main risk factor correlated with the occurrence and progression of atherosclerosis, cardiovascular disease (CVD), and stroke [1, 2]. As CVD remains a major cause of morbidity and mortality globally, the management of dyslipidemia is a key component of primary and secondary risk reduction strategies [3]. Statins, as the first-line therapy for dyslipidemia recommended by international clinical practice guidelines, can significantly reduce the risk of cardiovascular events [4, 5]. Nevertheless, statins are also associated with various adverse reactions such as hepatobiliary disorders, renal disease, myalgia, myositis, and rhabdomyolysis; long-term use of statins may increase the risk of incipient diabetes and cognitive dysfunction [6–11]. Other drugs such as fibrates also have similar adverse reactions, including liver toxicity, renal toxicity, and myopathy [12]. The management of dyslipidemia still remains a major challenge for patients who cannot tolerate the side effects of these classic lipid-lowering drugs (LLDs). Therefore, it is important to seek effective and safe alternatives to these LLDs.

Berberine (BBR) is an isoquinoline alkaloid isolated from various Chinese herbs, including Rhizoma coptidis (huanglian), Cortex phellodendri (huangbai), and Hydrastiscanadensis (goldenseal) [13]. It was initially used for the treatment of gastrointestinal infection. In recent years, a number of studies have suggested that BBR has a variety of pharmacological properties, such as antibacterial, antitumor, controlling arrhythmia, lowering blood lipids, lowering blood pressure, lowering blood glucose, and promoting islet cell regeneration [14–18].

The lipid-lowering effect of BBR has been supported in several studies. Kong et al. [17] reported that compared with placebo, oral BBR 0.5 g twice daily reduced the serum TC by 29%, TG by 35%, and LDL-C by 25%. Moreover, BBR combined with simvastatin showed enhanced lipid-lowering effect compared with monotherapy: the serum LDL-C was reduced by 31.8%, and reductions in TC and TG were also observed [19].

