Occasionally, oral or intravenous BBR may cause adverse reactions such as nausea, vomiting, constipation, hypertension, respiratory failure, and paresthesias. Rare adverse effects including headache, skin irritation, facial flushing, headache, and bradycardia have also been reported [20]. The therapeutic dose of BBR (0.5 g) is generally safe and well-tolerated, and gastrointestinal reactions are most often caused by overdose (≥ 4 g).

A recent systematic review and meta-analysis demonstrated that BBR could significantly reduce the levels of TC, LDL-C, and TG in patients with dyslipidemia [13]. Unfortunately, these studies were limited by their high heterogeneity and high risk of biases. Kong et al. [17] proved that BBR treatment significantly improved lipid profiles; however, the randomization, blinding procedure, sample size calculation, and detailed inclusion and exclusion criteria have not been mentioned, and a lack of restriction on the other medications could have influenced the results. As there has been a lack of large-scale, high-quality randomized controlled trials on this possibility at the population level, this randomized, double-blind, placebo-controlled clinical trial was designed to determine the lipid-lowering efficacy and safety of BBR in treating dyslipidemia.

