#### Blinding and unblinding procedures

A two-level blinding design will be used, with the first level being by group (group A and group B) according to case number and the second level by treatment (BBR and placebo).

The random code list will be created by a statistical agency, the two-level treatment codes will be sealed separately in duplicate, with a copy being kept by DHABUCM and the National Drug Clinical Trial Institution. Treatment allocations will be blinded to the participants, clinicians, research assistants, drug managers, statisticians, and other staff members and will not be revealed until the study is completed. The study would have been considered invalid if any treatment code disclosure arose from any non-prescribed circumstances and if it affected the objectivity of the data obtained from the study.

Whether the drug packaging meets the requirements of a double-blind clinical trial will be checked, and the drug quality inspection report will be created. The entire drug coding process is documented by the blind editor, as part of the documentation for the clinical trial. Each coded test drug will have a corresponding emergency letter, describing the subject’s medication, treatment methods, organization, and address to which requests for emergency unblinding should be immediately reported. The coded drugs will be sent to the study center together with the corresponding emergency letters.

In case of emergency (such as serious adverse reactions), or when the patient needs to be rescued and must know what kind of treatment the patient has received, the corresponding emergency letters shall be opened with the presence of the investigators and the administrator of research organization. Once the emergency letter is opened, the numbered subject will withdraw from the study. The investigators will record the reason in the case report form (CRF). All emergency letters will be collected with the CRFs for blind review at the end of the trial.

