### Outcomes

#### Primary outcome

The primary outcome is the percentage change in LDL-C from baseline at week 12.

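### The 4-week cardiovascular exclusion admits people soon after an infarction, stent, bypass or stroke, who can then be on placebo without a statin for 12 weeks

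*Protocol article*

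**What the plan says.** The Pharmacologic treatments section of the Protocol article sets the rule on other treatment: "Any lipid-lowing therapy except for the experimental drugs will be banned or restricted during the study". The article does not say whether the ban or the restriction applies, or to whom. The same section fixes the duration: "BBR or placebo will be administrated orally for 12 weeks". Allocation is 1:1 (Design).

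The Exclusion criteria treat infarction, stenting, bypass and stroke as disqualifying only when they are no more than 4 weeks old. A separate item excludes severe or life-threatening disease, without defining it. The Inclusion criteria require LDL-C of at least 4.1 mmol/L and/or TG of at least 2.3 mmol/L, and no lipid-lowering drug for 1 month. Neither list asks that the person be unable or unwilling to take a statin.

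On the treatment being withheld, the Background says: "Statins, as the first-line therapy for dyslipidemia recommended by international clinical practice guidelines, can significantly reduce the risk of cardiovascular events". It also says that "the management of dyslipidemia is a key component of primary and secondary risk reduction strategies". Its reason for seeking an alternative is a particular group: "The management of dyslipidemia still remains a major challenge for patients who cannot tolerate the side effects of these classic lipid-lowering drugs".

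**The concern.** Each rule is unremarkable alone; the difficulty lies in their combination. A short look-back for cardiovascular events admits people in secondary prevention. The rule on other treatment then asks them to go without the drugs that the Background credits with reducing events, and half of them receive placebo.

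The Background's case for the trial rests on patients who cannot tolerate the standard drugs. Since the criteria do not select such patients, intolerance cannot be assumed as the justification for withholding a statin from a given participant. What is at stake is the safety of a few individuals, not the validity of the primary comparison.

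**Working it through.** The plan states no figure that is in dispute here. The check sets the rules side by side and adds up the time.

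**Inputs**
- Earliest entry after an event: just over 4 weeks (Exclusion criteria).
- Drug-free period before entry: 1 month (Inclusion criteria).
- Treatment period: 12 weeks; the last visit has a window of ±3 days (Pharmacologic treatments; Table 1).
- Allocation: 1:1 (Design).

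**Step 1: can such a person enter?** Take someone 5 weeks after an infarction with LDL-C of 4.1 mmol/L, no lipid-lowering drug for a month and no other exclusion. The event is older than 4 weeks, so it does not exclude. The lipid threshold and the drug-free month are met, and intolerance is not asked for. As written, the person is eligible.

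**Step 2: how long without treatment, if other therapy is banned?**
- Earliest entry: just over 4 weeks + 12 weeks = just over 16 weeks after the event.
- Entry at week 5: 5 + 12 = 17 weeks after the event.
- Either figure can shift by 3 days with the visit window.
- At the earliest entry, the required drug-free month covers practically all the time since the event. The person has therefore had almost no lipid-lowering drug since then.

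**Step 3: chance of placebo.** With 1:1 allocation it is 1/(1 + 1) = 0.5. A participant allocated to berberine also goes without a statin, but receives the active study drug.

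**Step 4: does another criterion close the gap?** The item on severe or life-threatening disease could be applied to some of these people at the investigator's discretion. It is undefined, however, and it stands beside an explicit 4-week limit for exactly these events. The specific limit implies that older events are acceptable.

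**Step 5: how many?** The document gives no basis for a count. The person must have had an event, be outside the 4-week window, have been untreated for a month, meet a lipid threshold and have no diabetes or renal insufficiency. Few of the 118 are likely to fit.

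**The case against.** **Few or none may be affected, and they may have their reasons.** Someone still untreated a month after an event may well be intolerant of statins or have declined them, which is the group the Background describes. This stands as a limit on the size of the point. It does not remove the point, because the criteria neither require nor record such a reason for entry.

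**The look-back might apply to stroke alone.** The natural reading applies the 4 weeks to the whole list. On the narrow reading any earlier infarction, stent or bypass excludes, and the gap shrinks to strokes more than 4 weeks old.

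**The rule may be milder than a ban.** An article condenses the full protocol, and the wording may summarise a list of prohibited and restricted treatments. If that list lets a clinician start a statin in secondary prevention, the untreated period would be shorter than calculated. This stands too: the 16 weeks is what the text allows under a ban, not what must happen.

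**A stronger reading is tempting.** A reader might infer that a restriction, as opposed to a ban, lets newly started drugs distort the primary result. The outcome is exposed in principle: "The primary outcome is the percentage change in LDL-C from baseline at week 12". The Background also faults an earlier berberine trial because "a lack of restriction on the other medications could have influenced the results". The document does not support that inference, for three reasons:
- The unseen list may prohibit lipid-lowering drugs outright and restrict only other measures, in which case no new drug is permitted.
- The criticised trial lacked restriction. This one imposes some, records every drug taken and compares concomitant medication between groups.
- Neither size nor direction of bias can be derived. The planned difference is 25 − 5 = 20 percentage points. If fractions f_P (placebo) and f_B (berberine) start a drug with additive effect e, the difference becomes 20 − e·f_P + e·f_B, which is still 20 when f_P = f_B. Unequal starts are conceivable, but the plan gives no use rate, no effect of another drug alone and no SD.

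**Conclusion.** The point holds as a patient-safety matter of limited reach. Followed as written, the criteria can place a person just over 4 weeks after a cardiovascular event on placebo, with probability 1 in 2, and keep that person off lipid-lowering drugs until just over 16 weeks after the event. The plan's own Background argues against doing so.

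This rests on two assumptions: that the 4-week limit applies to the listed events as it naturally reads, and that other lipid-lowering therapy is banned, or restricted tightly enough to keep a statin from being started. The number affected is unknown and probably very small. No bias in the week-12 LDL-C comparison and no loss of power is shown. It ranks as a cheap improvement.

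**What to change.** 1. **Exclusion criteria:** exclude any history of myocardial infarction, stenting, bypass surgery or ischaemic stroke. Keep the present 4-week exclusion for any other stroke.
2. **Pharmacologic treatments:** state that a clinician may start lipid-lowering therapy when it is clinically necessary, and that the start is recorded as a protocol deviation. This also covers people who are already enrolled, since Trial status reports that recruitment is under way.

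The Statistical analysis section already retains participants in the full analysis set on the intention-to-treat principle and limits the per-protocol set to those who adhered, so no new rule on analysis sets is needed. How LDL-C measured after such a start is analysed can be left to the statistical analysis plan, which is not at hand.

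**Cost:** a formal amendment with ethics approval (Protocol amendments), a slightly narrower population, and results that do not apply to secondary prevention. Little recruitment should be lost, because few people are still untreated a month after such an event.

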### Outcomes

#### Primary outcome

The primary outcome is the percentage change in LDL-C from baseline at week 12.

#### Secondary outcomes

The following are the secondary outcomes:
Lipid profiles: TC, TG, HDL-C, and LDL-C will be measured at baseline (visit 1) and weeks 4 (visit 2), 8 (visit 3), and 12 (visit 4).Hs-CRP, BP, and body weight will be measured at baseline (visit 1) and weeks 4 (visit 2), 8 (visit 3), and 12 (visit 4).BSC: the participants will be asked “which type of stool they have” at each visit during the treatment period.TCM symptom form (according to the Clinical Research Guidance of New Investigational Drug in TCM [25]) will be evaluated at baseline (visit 1) and weeks 4 (visit 2), 8 (visit 3), and 12 (visit 4).Adipokine profiles [fibroblast growth factor 21 (FGF21), adiponectin (APN), hormone-sensitive lipase (HSL)] will be assessed based on the blood specimens collected at baseline (visit 1) and week 12 (visit 4).Intestinal microbiota will be analyzed by the metagenomics based on the stool specimens collected at baseline (visit 1) and week 12 (visit 4).

#### Safety assessments

The following are the safety assessments:
General physical examinationBlood and urine routine tests, ALT, AST, BUN, and CrAdverse events

#### Adverse event monitoring

When a serious adverse event happens, investigators must fill out the “SAE form” and report it to the major investigator and center ethics committee immediately. The event should be reported to the safety supervision division of the State Food and Drug Administration within 24 h.

The major investigator must offer corresponding treatment according to the drugs and symptoms, then record and sign at the CRFs in detail. The inspector must be informed of the treating processes.

All adverse events should be recorded in time and tracked until properly resolved or stabilized. Abnormal indexes in physical and chemical examinations should be checked until normal.

#### Participant timeline

The timeline for participant registration, intervention, and assessment is shown in Table 1, based on the Standard Protocol Items: Recommendations for Interventional Trials (SPIRIT) guideline (Additional file 1).

**Table 1 Tab1:** Content of data capture

Research stage	Baseline	Treatment period		
Item	0	4 weeks ± 3 days	8 weeks ± 3 days	12 weeks ± 3 days
Visiting no.	V1	V2	V3	V4
**Demographic data/baseline**				
Inclusion/exclusion criteria	√			
Informed consent	√			
History of disease and treatment	√			
Physical examination	√	√	√	√
Complications and concomitant medications	√			
**Outcome assessments**				
Lipid profiles	√	√	√	√
Hs-CRP	√	√	√	√
Blood pressure	√	√	√	√
Body weight	√	√	√	√
Bristol Stool Chart	√	√	√	√
TCM symptom form	√	√	√	√
Adipokine profiles	√			√
Intestinal microbiota	√			√
**Safety assessment**				
Blood routine measurements	√			√
Urine routine measurements	√			√
Liver function (ALT, AST)	√			√
Kidney function (BUN, Cr)	√			√
Adverse events	√	√	√	√
**Others**				
Randomization	√			
Drug distribution	√	√	√	
Drug recycling and counting		√	√	√
Record concomitant medications		√	√	√
Study conclusion				√

√: item need to be done during different period

#### Data collection

Laboratory parameters will be used for validity and safety assessments (see Table 1 for details). At the beginning of the clinical study, a detailed description about the biological specimen collection manual will be provided to researchers. Lipid profiles, hs-CRP, blood and urine routine, ALT, AST, BUN, and Cr will be measured by the laboratory department. For adipokine profile assay (FGF21, APN, HSL), 5 ml whole blood will be taken and kept at room temperature for 0.5 h. Centrifugation will be performed by 3000 r min^−1^ at 4 °C for 10 min, and the separated serum will be collected into cryopreservation tubes for storage at − 80 °C. Stool specimens in the size of soybeans will be placed into dry, sterile collection tubes and stored at − 80 °C for cryopreservation. Biological specimens collected in the study will be stored in the biological sample bank of DHABUCM.

#### Data management and quality assurance

Before the conduction of the clinical trial, all investigators and relevant staff including clinicians, research assistants, and drug managers will be uniformly trained regarding the trial-specific process. Investigators will fill in the CRFs according to the subjects’ hospitalization records and original observation records. All collected data will be checked regularly by the inspectors so as to avoid mistakes and omissions. Original record of any modification shall be clearly visible, and the corrections shall be signed and dated by the investigator. And then, the CRFs shall be submitted to the clinical trial data administrators. This transfer process between investigators, inspectors, and data administrators needs to be recorded and saved. Data will be checked again by the data administrator before data entry. Any questions and answers will be kept as query tables for future reference.

Double data entry of CRFs will be conducted independently. The data manager should check the database with the major investigator for data scope and logical content. After data entry and verification as required, the original CRFs shall be archived and saved in order, and filled with the search catalog. Electronic data files including databases, inspection procedures, analysis procedures, analysis results, codebooks, and description files, should be stored in categories, and multiple backups should be saved properly on different record media. All the original files shall be kept within the prescribed period according to China’s Drug Clinical Trial Quality Management Standard.

#### Sample size calculation

The sample size for this trial was calculated based on the primary outcome using the PASS 11.0 (NCSS LLC, Kaysville, UT, USA) software. According to the previous results of berberine on dyslipidemia [17, 26], the percentage reduction in LDL-C (the primary outcome) is 25% in the berberine group and 5% in the placebo group. Forty-seven patients in each group can achieve 80% power and rule out type I error of 5% by using a two-sided test. We expect that 20% of the participants may be lost to follow-up. Therefore, the sample size in each group should be adjusted to 59. In total, 118 participants will be enrolled in this trial.

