### Design

This is a study protocol for a randomized, double-blind, placebo-controlled clinical trial with a treatment period of 12 weeks, which will be conducted between April 2019 and December 2020. Eligible patients will be randomized at a ratio of 1:1 into either the BBR group or the placebo group. The protocol was developed according to Consolidated Standards of Reporting Trials (CONSORT) statement [21], Standard Protocol Items: Recommendations for Interventional Trials (SPIRIT) 2013 [22], and SPIRIT 2013 explanation and elaboration: guidance for protocols of clinical trials [23]. A total of 4 visits will be scheduled at baseline (visit 1) and weeks 4 (visit 2), 8 (visit 3), and 12 (visit 4) to assess treatment efficacy, safety, and adverse events. This 12-week treatment period was set based on our clinical experience and previous pilot studies [13, 17]. Additionally, potential predictive factors involving patient and disease characteristics have been collected in a comprehensive manner. Figure 1 shows the flow diagram of the trial.

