#### Statistical analysis

Statistical analysis of all data will be performed by a dedicated statistician in a blinded manner. All statistical analyses of the data will be performed using the SAS 6.12 (SAS Institute Inc., Cary, NC, USA) software.

The analysis data set will consist of a full analysis set (FAS), a per-protocol set (PPS), and a safety set (SS). FAS: according to the principle of analysis for intention to treat (ITT), participants will be rejected by the smallest and reasonable method. The last observation carried forward (LOCF) method will be used for the missing data supplement. The PP data set will include only participants who adhered to the study protocol and completed the clinical study. The minimum compliance rate for participants taking the investigational drugs in the PP data set is 80%. The SS will include information on safety records, including adverse events and laboratory test results. Quantitative indices recorded will include the numbers of cases, mean ± SD, median, and maximum and minimum values; qualitative or grade indices will be recorded using frequency and percentage. Two-sided tests will be used in all cases, and *P* ≤ 0.05 will be considered to be statistically significant.

From baseline to each time point, discrete variables will be described with frequencies and percentages, and continuous variables will be described with either mean and standard deviation for data with normal distribution or median and interquartile range for non-normally distributed data. For comparisons between the experimental and control groups at each time point, a chi-square test or Fisher’s exact test will be used for discrete variables, and Student’s *t* test or the Wilcoxon-Mann-Whitney *U* test will be used for continuous variables.

The analysis of concomitant medications will be analyzed by the chi-square test or Fisher’s exact test. The analysis of treatment compliance should include both the experimental drug and the basic treatment, and the chi-square test/Fisher exact probability method will be used for comparison.

All adverse events during the trial should be described in the form with the type, severity, and relationship with the experimental drug. Adverse events will be classified into all adverse events and related adverse events, among which, for conservative consideration, will include “definitely related,” “probably related,” “possibly related,” and “suspected related” to the drug.

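### The 47 per group appears to come from treating mean LDL-C reductions of 25% and 5% as response proportions, so the stated 80% power is not established for the continuous primary outcome

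*Protocol article*

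**What the plan says.** Under Primary outcome, the protocol article states: "The primary outcome is the percentage change in LDL-C from baseline at week 12". This is a continuous measure taken on each patient. Under Statistical analysis, "Student’s *t* test or the Wilcoxon-Mann-Whitney *U* test will be used for continuous variables" in the between-group comparisons at each time point.

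Under Sample size calculation, the article says that the number was derived for the primary outcome in PASS 11.0. The assumption, taken from two earlier studies, is that "the percentage reduction in LDL-C (the primary outcome) is 25% in the berberine group and 5% in the placebo group". The next sentence gives the result: "Forty-seven patients in each group can achieve 80% power and rule out type I error of 5% by using a two-sided test". A 20% loss to follow-up then raises 47 to 59 per group, 118 in total. The paragraph gives no SD and no standardised effect, and names neither the test nor the PASS module.

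The Background shows what kind of quantity the 25% is. It reports, for one of the two studies cited in the sample size section, that "oral BBR 0.5 g twice daily reduced the serum TC by 29%, TG by 35%, and LDL-C by 25" per cent. That is a fall in a lipid level. The article defines no LDL-C responder anywhere.

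**The concern.** A sample size for comparing two means needs the difference and the SD. A sample size for comparing two proportions needs only the proportions, because they fix the variance. The paragraph supplies two percentages and nothing else, yet arrives at a definite number. That suggests a calculation for a binary endpoint that the trial does not have.

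If so, the 80% describes a test that will not be run. The power of the planned comparison, and the difference the trial can reliably detect, then depend on an SD that played no part in the calculation. The number of patients randomised rests on this one paragraph. The article also criticises an earlier berberine trial in its Background for not reporting a sample size calculation, so its own should hold.

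**Working it through.** **Inputs from the article.** 25% and 5% (difference 20 points); two-sided alpha 0.05; power 80%; allocation 1:1; loss to follow-up 20%. The SD of percentage change in LDL-C is not given, so the range used below is an assumption.

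**1. Reproducing the stated figure as two proportions.** With p1 = 0.25 and p2 = 0.05, the unpooled normal formula is

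n = (1.960 + 0.842)² × [p1(1 − p1) + p2(1 − p2)] / (p1 − p2)²

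= 7.849 × (0.1875 + 0.0475) / 0.04 = 46.1, rounded up to 47.

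Power by this formula is 79.9% at 46 and 80.7% at 47, so 47 is the first whole number to reach 80%. Other two-proportion variants do not match: pooled variance gives 48.8, so 49; arcsine gives 44.2, so 45; the continuity-corrected version gives 59.

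**2. Dropout step.** 47 / (1 − 0.20) = 58.75, rounded up to 59; 2 × 59 = 118. This step is correct.

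**3. The SD that a comparison of means would need.** For a two-sample t test with a 20-point difference and 47 per group, power is 80% when the SD is 34.2 points. The SD implied by treating 25% and 5% as proportions is √[(0.1875 + 0.0475)/2] = 0.343, or 34.3 points. The two agree closely, as they must if the number came from proportions.

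**4. Power of the planned type of comparison.** Two-sample t test, two-sided 5%, by assumed SD. The power and sample size columns take a true difference of 20 points.

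| Assumed SD (points) | Power, 47 per group | n per group for 80% power | Difference detectable with 80% power, 47 per group |
|---|---|---|---|
| 15 | >99.9% | 10 | 8.8 |
| 20 | 99.8% | 17 | 11.7 |
| 25 | 97% | 26 | 14.6 |
| 30 | 89% | 37 | 17.5 |
| 35 | 78% | 50 | 20.4 |
| 40 | 67% | 64 | 23.4 |

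**5. If all 59 per group are analysed.** The full analysis set follows intention to treat with last observation carried forward (LOCF), so the analysed number may exceed 47. At 59 per group, and if carrying values forward does not dilute the 20-point difference, power is 87% at SD 35 and 77% at SD 40.

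**The case against.** The article does not say which test or PASS module was used, so the use of a two-proportion formula is inferred. A means calculation is not excluded: a t test with a 20-point difference and a round SD of 34 needs 46.3, also 47 per group. The match to proportions holds only for the unpooled version. This much stands, and the point is therefore worded as an appearance. The proportions route is still the simpler explanation, since it needs only the printed figures, while the means route needs an unprinted SD that happens to fall next to the binomial one.

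It can also be said that an article may leave the SD to the full protocol. A missing SD alone would be a weak point. Here, however, the printed inputs reproduce the printed result for a binary comparison, while the outcome and analysis sections describe a continuous one. That is a mismatch within the article.

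A reader might infer that the trial is too small. The document does not support this: no SD is given, and at 47 per group power for 20 points is 89% or more for SDs up to 30, dropping below 80% only above about 34. A reader might also infer that a null or small result could not be interpreted. That does not follow either, because a completed trial is read from its estimate and confidence interval, using the observed SD.

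**Conclusion.** The concern holds as a strong inference. The sample size appears to treat two mean percentage reductions as response proportions, and the stated 80% power is not established for the continuous primary outcome. It would hold for a 20-point difference at 47 per group only with an SD of about 34 points. Across assumed SDs of 15 to 40 points, power at 47 per group runs from over 99.9% to 67%, so the error could lie in either direction. These figures rest on a t test, equal SDs in the two groups and a true difference of 20 points.

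This should be corrected but is not critical. It affects the justification of the sample size. It does not bias the treatment estimate or inflate the type I error, and no loss of power has been shown.

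**What to change.** Keep N = 118 and replace the sample size paragraph with a two-sample comparison of means for percentage change in LDL-C. State the SD and its source (the two cited studies, if they report a usable one), and add a short sensitivity range. Restate the power for a 20-point difference and the difference detectable with 80% power for 47 completers per group. As a guide, the latter is 8.8 points at SD 15, 11.7 at SD 20 and 23.4 at SD 40.

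If an SD near 34 was in fact used, printing it with its source and naming the test resolves the point. If a responder endpoint was intended, define it and reconcile the Primary outcome section with the sample size section.

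The cost is one rewritten paragraph. The rewrite itself adds no patients and changes neither the endpoint nor the planned test. The stated power will change unless the SD is near 34 points, and an SD above that would show power below 80% at 47 per group, which the sponsor would need to know.
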